#### 8.3.5. *Description of the questionnaires and interviews*

All questionnaires can be found in section F1 of the standard research file.

##### ***Patient population***

A set of standardized, validated questionnaires will be used to describe the characteristics of the patients included in the trial. This set includes the falls efficacy scale international (FES-I) , the dizziness handicap inventory (DHI) , the oscillopsia severity questionnaire (OSQ)  and the hospital anxiety and depression scale (HADS) . These questionnaires quantify the severity of the different symptoms associated with BV and a utility based QoL assessment.

Furthermore we will also incorporate a BV specific questionnaire which is still under development within our group (aimed to be completed around the start of 2021). This questionnaire is based on interviews with  and focus groups of BV patients. It aims to characterize all aspects of how BV affects a patient's life and well-being (manuscript in preparation). Although the scope and formulation of the questions included in this questionnaire are expected to stay the same, the selection of questions still has to be finalized. The resulting questionnaire is expected to be about half of the one currently submitted in section F1 of the standard research file.

##### ***HTA***

To allow for the calculation of quality adjusted life years (QALYs) related to receiving a CVI, a set of questionnaires are included at several time points throughout the trial. These questionnaires include the euroqol five-dimensional questionnaire (EQ5D-5L) , the icepop capability measure for adults questionnaire (ICECAP-A)  and the health utility index mark 3 (HUI-3) . These questionnaires will be administered before implantation, after CI rehabilitation and during the VI stimulation period to assess both the influence of the CI and the VI part of the CVI device. The QALY calculations will be valuable for the creation of a HTA, exploring the feasibility of a CVI device from a societal and economic standpoint.

##### ***Hearing***

Complementary to the objective hearing related outcomes, also a patient reported hearing questionnaire will be administered during the different CI rehabilitation and follow-up visits: the speech spatial and qualities of hearing scale (SSQ-12) . By using both objective and subjective outcome measures to quantify CI functionality, a more complete characterization can be achieved.

##### ***Tinnitus***

To monitor any potential change in tinnitus due to CVI surgery the tinnitus questionnaire (TQ)  will be administered before and after surgery. A change in tinnitus severity (both positive and negative) is a common side-effect of CI surgery , which indicates the importance of quantifying tinnitus also during this trial.

**Daily VAS-based list of questions**

At this moment a specific measurement tool for quantifying the impact of a CVI on subjective outcome parameters has not yet been developed. To reduce the amount of questionnaires the patient has to fill in, and to be able to better quantify day-to-day differences in subjective outcomes during the prolonged stimulation period, a shorter, more specific, custom-made list of VAS based questions was created by our research team. This VAS-based list of questions aims to quantify the influence of the CVI on the self-perceived severity of BV and hearing loss related symptoms, alongside characterizing patient satisfaction with the CVI.

**Interviews**

At the end of the CI rehabilitation period, during the VI fitting period and the prolonged stimulation weeks semi-structured interviews will be conducted with the patients. The goal of these interviews is to collect patient experiences on the use of the CVI and obtain expectations about the potential benefit of the CVI in daily life. Although less structured and quantifiable than questionnaires, these interviews will allow us to characterize more subtle and personal changes. Furthermore, the patient perspective will be valuable for substantiating the claim of further developing the concept of VI stimulation.

**Rehabilitation**

To give more structure to the rehabilitation program which is included in the prolonged stimulation period, the patient-specific functional scale (PSFS)  questionnaire will be used to set and monitor patient-specific training goals. The goals will be characterized both before using the VI-functionality of the device and during the prolonged stimulation period.

**8.3.6. Description of the trial visits**

A detailed overview of the trial planning can be found in chapter 3, table 1.

**Inclusion**

At the ENT department of the MUMC+, every patient that is believed to suffer from a balance disorder or is candidate for cochlear implantation, undergoes a screening of his or her vestibular function by means of bilateral caloric test as part of the standard clinical routine. This has resulted in a large cohort of patients on a “VI-waiting list” that could be eligible for and have indicated to be interested in taking part in the next VI study, and patients are still being added to this list. All these patients gave consent to be contacted by one of the research team members, which was written down in the clinical patient file.

When ethical approval is obtained, one of the members of the research team will contact the patients on this “VI-waiting list” either via email or post. The patient will be asked whether they want to receive more information regarding this specific study. If so, the patient information brochure will be sent to the patient via post. If a patient who is in the clinic for a regular visit appears to be eligible for participation in the trial, the patient will be informed about the trial by their doctor or audiologist. If the patient is interested in learning more about the trial, the patient information brochure will be handed to the patient in person. Via the patient information the patient will be informed that he or she can contact an independent physician or the members of the research team if the patient has any questions. The patient will be asked to reply either by email or telephone. If the patient is interested in participating, a meeting will be

scheduled with a member of the research team (who is not the primary physician) to discuss the patient information, to allow the patient to ask questions and to sign the informed consent form. Every candidate will have at least 2 weeks to think about taking part in the study after receiving the patient information brochure.

After obtaining the candidate's written informed consent, a complementary extensive vestibular examination will be done. This VI-inclusion visit will consist of a list of standard vestibular examination tests which are daily, routinely used to investigate the vestibular function in patients with balance disorders. The tests which are included in this list are the caloric test, the oVEMP, the cVEMP, a 3D HIT and a torsion swing test. One extra test, specifically related to the CVI study, will be added: the DVA test. A description of these tests is given in chapter 8.3.1. The complete VI-inclusion visit includes around 3 hours of testing, unless patients were already extensively tested as part of their diagnostic work-up for their pathology. If so, all previously performed tests will be skipped and the VI-inclusion visit will take less time.

Alongside this, a standard CI inclusion procedure will be conducted to assess the patient's eligibility for receiving a CI in the ear to be implanted. This includes hearing tests, an ENT consult and visits to an audiologist, a speech therapist and a social worker. Also an MRI and a neuronavigation CT scan will be made. Any CI eligibility testing that might have been done before as part of regular clinical care will not be repeated.

If the patient meets all inclusion criteria and none of the exclusion criteria as described in chapter 4.2 and 4.3, the patient will be included in the trial. A total of 8 patients will be included. A date will be assigned for the surgical procedure and the patient will be given a set of questionnaires to be filled in at home.

***The surgical procedure (performed under general anesthesia):***

1. Routine retro-auricular approach
2. Routine mastoidectomy and posterior tympanotomy (as performed in cochlear implant surgery)
3. Human fascia is harvested from the temporal muscle
4. The bed for the receiver is drilled (as performed in cochlear implant surgery)
5. The SSCs are blue-lined using the ampullar "V"-approach
6. The round window is drilled and opened to facilitate cochlear implantation
7. The cochlear electrode is implanted using the round window approach
8. Electrodes are implanted in each canal:
  - a. The canal is fenestrated near the ampulla
  - b. The electrodes are inserted in the canal to reach the ampulla
  - c. Fluoroscopy is used to optimize the electrode positioning
  - d. 3D-CT scanning is performed and images are fused with the preoperative CT scan and MRI to verify the electrode positioning. If necessary, electrodes are repositioned using fluoroscopy. If necessary, a second 3D-CT scan is performed to check the electrode positioning after repositioning.
  - e. The electrodes are fixed using 3M™ Ketac™
  - f. A final 3D-CT scan is performed to assess electrode positioning after fixation.

- g. The fenestration is closed with bone pate and the harvested fascia
- 9. The receiver is fixated (as performed in CI surgery)
- 10. The wound is closed in three layers (as performed in CI surgery)
- 11. Structural integrity is checked as performed in CI surgery by performing ART and impedance measurements. Stimulation potency is checked by performing a function test of the vestibular electrodes: during stimulation, VOR is recorded using videogoggles.
- 12. A standard head dressing is applied
- 13. The procedure is completed and the patient wakes up
- 14. One night is spent in hospital and the next day the head dressing is removed and the patient is discharged from hospital (as in CI surgery)
- 15. One week post-operatively, the stitches are taken out, the healing cap is removed and the wound is checked at the outpatient department (as in CI surgery)

### ***Post-operative period***

Around 1 week after surgery (combined with the ENT post-surgery check-up) the patient will undergo a CBCT scan in order to evaluate the location of the electrodes in the ampullae and cochlea. The patient will also be asked to fill in the TQ questionnaire.

### ***CI rehabilitation***

CI rehabilitation will be performed as standard in our clinic. This includes a minimum of 11 visits (can be individually extended if necessary) in the time-span of 3 months to establish a fitting and to train the patient with using their CI. The CI rehabilitation period starts around 1 month after implantation. During the first visit a first fitting will be established and the patient will receive their standard CI processor (described in chapter 7), which will be connected to the CVI implant.

Each of the CI rehabilitation visits will take between 1 and 2 hours. During each CI visit, the impedances of all VCI electrodes will be checked. On top of that a short functional test of the VI electrodes will be introduced. This functional VI test will first be piloted in one subject. If the procedure is accepted, the intention is to repeat this functional VI test for each of the upcoming subjects as an extended part (max 60 min.) to three of the regular CI visits. This functional VI test will entail a short, maximum 2 seconds, stimulation of the VI electrode in each of the SSC, starting low in amplitude and increasing in small steps. To generate this stimulation the CI fitting software Maestro will be used. After each stimulation the patient will be asked if they felt something, what they felt and if it is comfortable. As soon as the patient experiences the stimulation as uncomfortable, the test will be stopped. Aside from the subjective feedback, also the eye movements will be captured objectively using video goggles. At no time during this function VI test, or any other moment during CI rehabilitation, the AMP processor will be turned on. The only time patients will actively use the AMP processor is during the VI fitting period and the prolonged stimulation period while they are being supervised in the hospital by the research team.

The final CI fitting visit, 3 months after the start of the CI rehabilitation period will include extra trial related procedures in addition to regular CI procedures. At this point ART measurement will be performed. Also cervical and ocular VEMPs are measured, if they were not absent during inclusion. Alongside this a SPIN hearing test is performed and the patient is asked to fill in questionnaires.

***VI fitting***

An example of the VI fitting schedule can be found in chapter 3, table 2. Just as with a regular CI, a fitting will have to be established for the VI part of the CVI. During the fitting the correct minimum and maximum current levels at which to stimulate the vestibular nerves will be established. This will only be done once the intensive CI rehabilitation is completed and a stable CI fitting is established (i.e. circa 4 months after implantation). During this trial, for the first time in the context of VI research by the Geneva-Maastricht group, three VI electrodes will be combined with simultaneous CI stimulation. Therefore we have allocated 4 days to establish a fitting of the full CVI, allowing for an accurate fitting process including an ample amount of breaks to keep the burden on the patient as low as possible. Especially when the VI electrodes are stimulated for the first time, the patients perceive it as a strange experience which they have to get used to. During the fitting procedure patients will be staying in a hotel next to the hospital, to reduce the burden of traveling. Also breakfast, lunch and dinner will be paid for. If the patient prefers to distribute the fitting days into a larger period (for example 2 days of fitting per week for 2 weeks), this will also be possible. Although we believe 4 days is more than sufficient to create a CVI fitting, due to its novelty, in specific cases it might be necessary to add another day of fitting. This will be reported upon in the trial master file as a protocol deviation.

The goal of the fitting is to establish for each of the vestibular electrodes the threshold (T) of stimulation which yields a vestibular response and the upper limit of stimulation which is comfortable (UCL) for the patient. The T level will be based on perception, VOR or VSR, whichever occurs at the lowest stimulation current. UCL is defined as the lowest current level at which either stimulation becomes no longer comfortable for the patient based on a VAS scoring system, the stimulation elicits unwanted responses (e.g. tickling, stimulation of the facial nerve or pain) or the maximum safe current that can be supplied by the implant is reached. The range between these two points is called the dynamic range (DR), and establishing a DR for each electrode is the same as what is done during a regular CI fitting. The fitting of each VI electrode will be done in two stages to fine-tune the fitting, as shown in chapter 3, table 2. Due to current spread, the amount of current reaching certain nerves might be higher with combined stimulation than with individual stimulation. Therefore, the last step in the fitting process is to evaluate the UCL of all electrodes during combined stimulation, adjusting stimulation levels if necessary. Also a hearing test will be conducted to evaluate CI performance while both the vestibular and cochlear electrodes are active.

During the fitting period an interview will be conducted with the patients to characterize in a structured way the patient's expectations of the CVI and how they describe their first experiences with vestibular stimulation. Also 1,5 hours will be reserved for a visit to the balance and gait lab in the hospital, to get acquainted with some of the tests that will be performed during baseline testing and the prolonged stimulation period. This will help ensure more accurate test results later on, besides allowing the patient to be introduced to the physiotherapists and motion scientists that will be working with them.

The fitting period will also be used to characterize the first responses of the vestibular system to electrical stimulation. These responses will be elicited by low level stimulation using a Costas array-based

stimulation sequence and recorded for stimulation optimization. It will be measured both at the start of the fitting period and at the end, to observe early adaptation processes to vestibular stimulation.

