Each day of CVI stimulation will start and end with impedance measurements and a check of UCLs. This is done as a safety precaution to make sure that the implant is performing as expected, even though it is expected that these parameters will not change during the prolonged stimulation period. These measurements will take only 5 minutes to complete. After this, one hour is reserved on Monday and half an hour on every following day to allow the patient to get used to the stimulation. Previous research by the Geneva-Maastricht group has shown that habituation to stimulation at 50% of the DR takes around 30 minutes for the first time the nerves are stimulated, and progressively less time at the start of each consecutive stimulation period. By taking this time every morning for the patient to get used to the stimulation, the reproducibility of the measurements will increase. At the start of every day the patients will also be asked if any (S)AE's occurred after leaving the hospital the previous day (i.e. attacks of nausea or vertigo). At the end of each prolonged stimulation day, the patients will be asked to fill in the VAS based list of questions to characterize their experiences with the CVI on a daily basis.

All the tests which will be conducted during the prolonged stimulation weeks are shown in table 4 of chapter 3 and described in chapter 8.3.1 through 8.3.5. All testing will occur during the four days of prolonged stimulation, except for three perception tests, one performed each Sunday afternoon before every period of prolonged stimulation. The patient will be asked to arrive in the hospital around 16:00 on Sunday for 1 hour of testing. The patient will be tested while using their regular CI processor. The goal of the tests is to assess if any change occurs in the baseline measurement after the patient has performed the perception platform test a few times. This is to exclude any chance that a learning effect might occur for the perception platform test, which is something that has not yet been fully studied. At the end of this test the patient will also be asked to fill in the VAS based preference scales.

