##### 13.1.4. *Selectivity of the mechanism*

Due to the CVI being based on electrical stimulation, current spread will occur. As the stimulation current increases, so does current spread, which may lead to stimulation of other nerves such as facial nerves or auditory nerves. The potential for stimulating nerves outside of the inner ear is reduced due to the way the stimulation parameters are chosen, setting the maximum stimulation currents below the current at

which unwanted stimulation occurs (see chapter 8.3.2). This is the same way as current spread is reduced with a CI. Part of the study is to safely investigate the presence of interfering current spread between the cochlea and the vestibular system. The interaction between vestibular and cochlear stimulation might (temporarily) result in a reduced CI or VI performance. The patient will be informed that CI performance might be reduced during simultaneous stimulation, since this might result in a burden to the patient. This will only be the case while the VI-part is active during the VI fitting period and the prolonged stimulation period. While optimizing the VI stimulation response during the VI fitting, the goal is to minimize the interaction between CI and VI stimulation and therefore minimize this burden.

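### The fitting rule in 8.3.6 puts the upper stimulation limit at the first uncomfortable or unwanted-response current, while 13.1.4 says the maximum is set below it (minor)

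*Protocol*

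**What the plan says.** Section 8.3.6, VI fitting, gives the purpose of the fitting: "During the fitting the correct minimum and maximum current levels at which to stimulate the vestibular nerves will be established". The next paragraph names the two levels sought for each vestibular electrode. One is the threshold T. The other is "the upper limit of stimulation which is comfortable (UCL) for the patient", which agrees with the abbreviation list, where UCL stands for Upper Comfortable Limit. The range from T to UCL is the dynamic range (DR).

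The same paragraph then gives the working definition: "UCL is defined as the lowest current level at which either stimulation becomes no longer comfortable for the patient". Two further criteria follow: "the stimulation elicits unwanted responses (e.g. tickling, stimulation of the facial nerve or pain", and reaching the largest current the implant can safely supply. Whichever occurs at the lowest current decides.

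Section 13.1.4, on selectivity, describes the safeguard against stimulating nerves outside the inner ear. It rests on "setting the maximum stimulation currents below the current at" "which unwanted stimulation occurs (see chapter 8.3.2" (one sentence, split by a page break).

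The UCL is used again during the stimulation weeks: "Each day of CVI stimulation will start and end with impedance measurements and a check of UCLs".

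**The concern.** The protocol defines the top of the stimulation range in two incompatible ways. The sentence that staff would follow at the fitting puts the limit at the first current that is already uncomfortable or already elicits tickling, facial nerve stimulation or pain. The risk analysis tells the ethics committee that maximum currents lie below the level of unwanted stimulation.

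Section 6.4.2 says this is the first use of the audio-motion processor to drive a CVI in humans. A current limit offered as a risk control should have one meaning in that setting. A reader who follows the pointer in 13.1.4 to check the rule arrives at the hearing tests in 8.3.2, not at the fitting procedure.

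**Working it through.** The plan gives no figure to reproduce here. The check compares the texts and then counts how often the rule applies.

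**1. Is the UCL the maximum stimulation current?** The first paragraph on VI fitting in 8.3.6 says the fitting establishes the minimum and maximum currents for stimulation. The second says it establishes T and UCL. Nothing else is established, so T is the minimum and UCL the maximum. No sentence in 8.3.6 sets the programmed maximum a margin below the UCL.

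**2. The unwanted-response criterion against 13.1.4.** Let U be the lowest current that elicits an unwanted response.
- 8.3.6, where this criterion decides: UCL = U, so maximum = U.
- 13.1.4: maximum < U.

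Both can hold only if delivered current is always kept below the UCL, which the protocol does not say. Section 1.4.4 describes modulating up and down to the same extent from a baseline at 50% of DR, and gaining room for excitation by lowering the baseline. Neither statement stops short of the top of the range. The prolonged stimulation text in 8.3.6 leaves the modulation level to be set after the fitting.

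**3. The comfort criterion.** Section 13.1.4 is silent on comfort, so this conflict lies within 8.3.6. Let C be the lowest uncomfortable current.
- Goal sentence and abbreviation list: the UCL is still comfortable, so UCL < C.
- Definition: UCL = C.

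**4. The safe-maximum criterion.** The implant's safe maximum is a permitted current, so this criterion raises no conflict. Two of the three criteria are affected: one against 13.1.4, the other against the goal sentence in 8.3.6.

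**5. Size of the difference.** If currents are tested in steps of size s, the first level with the effect and the last level without it differ by s. The protocol gives no step size for the fitting, so this cannot be expressed as a percentage of DR.

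**6. How often the rule is used.** Inputs: 3 vestibular electrodes (5.1.1), 8 to 13 patients (4.4), 4 stimulation days in each of 3 weeks, and a UCL check at the start and end of each day (8.3.6, prolonged stimulation period).
- Ceilings: 3 × 8 = 24; 3 × 13 = 39.
- Check sessions per patient: 2 × 4 × 3 = 24.
- Check sessions in all: 24 × 8 = 192; 24 × 13 = 312.

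These are planned maxima. Withdrawals, skipped activities (8.4) and unresponsive electrodes (10.4) would lower them. They count uses of the rule, not expected harms.

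**7. Cross-reference.** Section 13.1.4 cites 8.3.2, which describes the hearing tests. The fitting rule is in 8.3.6.

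**The case against.** The strongest reply is that the contradiction needs an inference. The UCL is the top of the dynamic range, no sentence says current is delivered at it, and baseline stimulation is at 50% of DR or lower. If delivery stays below the UCL, both sections hold. The first part is true: the protocol nowhere says modulation reaches the UCL. But it also states no margin, and it presents the fitting limits as the currents at which to stimulate. The reconciliation has to be supplied by the reader.

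Second, the highest comfortable and lowest uncomfortable levels describe one boundary from two sides, and the goal sentence shows what was meant. Staff will probably act on that meaning. This supports a minor grade but leaves two different currents as candidates for the programmed limit.

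Third, 13.1.4 concerns unwanted nerve stimulation, not comfort. That is correct, and the conflict with 13.1.4 is confined to the unwanted-response criterion.

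Fourth, the short functional test during CI rehabilitation adds little. There, "As soon as the patient experiences the stimulation as uncomfortable, the test will be stopped", but stopping at first discomfort is also how one would find the UCL as literally defined. That text fits either reading, and nothing here rests on it.

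Fifth, safeguards exist. UCLs are re-evaluated under combined stimulation and checked twice a day, use is supervised, and the patient can stop stimulation at once. Device details are deferred to a separate dossier not available here. The safeguards limit the consequences, but the repeated UCL checks use the same ambiguous definition.

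**Conclusion.** The point holds and is minor. Read literally, the definition in 8.3.6 gives a ceiling without the property that 13.1.4 claims for it, and it contradicts the description of the UCL in its own paragraph. The discrepancy is one tested current step of unstated size. It applies to up to 24 to 39 electrode ceilings and is carried into up to 192 to 312 planned check sessions. No quantified harm follows from the protocol.

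The conclusion assumes that the UCL is the programmed maximum, which is the natural reading of the two fitting paragraphs, and that no margin below it is fixed in a document not shown. The VI-ON versus VI-OFF comparison, the sample size and the trial's conclusions are unaffected.

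**What to change.** In 8.3.6, replace the definition with: the programmed UCL is the highest tested current below the first level that is uncomfortable or elicits an unwanted response, capped at the maximum safe current of the implant. State that this applies in both fitting stages, in the combined-stimulation evaluation, and in the UCL checks at the start and end of each stimulation day. In 13.1.4, change the cross-reference from 8.3.2 to 8.3.6.

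The cost is one reworded definition and one corrected reference in a protocol amendment, with no additional visits, tests or form fields.
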